## Abstract

Background: Children and adolescents should perform, according to the World Health Organization guidelines, at least 60 min of moderate-to-vigorous physical activity per-day in order to avoid the risk of metabolic and cardiovascular diseases. The school represents a fundamental setting to conduct interventions to promote physical activity (PA) and contrast sedentary behaviors. Active breaks (ABs), bouts of 10 min of PA conducted inside the classroom, seem to be a good strategy to promote PA and improve classroom behavior. The aim of this study protocol is to describe the design and the assessment of the Imola Active Breaks I-MOVE study. Methods: The I-MOVE study is a school-based intervention trial, with a quasi-experimental design, performed in a primary school. It involves one experimental-group performing the intervention, focused on ABs, and one control-group. Nine main outcomes are evaluated: PA and sedentary behaviors; health related fitness; motor control development; dietary patterns; anthropometric evaluation; sociodemographic determinants; cognitive function; time-on-task behavior and quality of life. Conclusions: Results from the I-MOVE study will help to clarify the effects of incorporating ABs in the Italian school curriculum as a new public health strategy and an innovative school model oriented to the well-being of children and teachers for the best quality of school life.

## 1. Introduction

Many studies report that regular physical activity (PA) during childhood is correlated with physical, mental, emotional and social health benefits [1,2]. According to the World Health Organization children and adolescents, aged 5–17, are recommended to perform at least 60 min of moderate-to-vigorous PA (MVPA) per day in order to avoid the risk of metabolic and cardiovascular diseases [3]. Furthermore, a poor amount of PA in children and adolescents are considered as a crucial risk factor for chronic diseases in adult life [4]. However, despite these recommendations, more than half of children and adolescents worldwide do not meet the recommendation of 60 min of MVPA per day [5,6] and it is estimated that in Italy only 9.5% of boys and 2.6% of girls achieve the daily amount of PA [7]. Currently, children and adolescents spend most of their time at school [8] this environment gives access to children regardless of age, ethnicity, gender, and socioeconomic class without any distinctions, and providing an inclusive place for everyone. Therefore, the school can be considered as an effective socializing context for health promotion interventions [9,10], especially to promote children’s good lifestyles and PA [11].

For this reason, schools should provide space, time, facilities and new strategies to encourage children to be physically active, helping to reach the 60-min per day of moderate-to-vigorous physical activity guideline [12]. Unfortunately, many school settings are not providing children with adequate opportunities to become physically active and may not generate enough PA in children and adolescents. Studies report that children and adolescents in European countries spend 65–70% of school hours in sedentary behaviors [13,14].

In this frame, we propose a quasi-experimental study to assess the feasibility and efficacy of a school-based intervention based on active breaks (ABs) to promote PA within the classroom context. ABs are 10–15 min bouts of MVPA activity incorporated in the school time, performed inside the classroom context and led by teachers during the academic lessons. Incorporating active breaks in the school day has been highlighted as a positive strategy for helping children in accumulating the required amount of PA [15]. ABs are also emerging as a promising way of increasing the PA levels, and reaching positive learning outcomes [16]. As suggested by a recent systematic review with a meta-analysis, ABs interventions have positive effects in increasing PA levels and improving classroom time-on-task behavior [17]. In particular, the evidence suggests that with 10 min thrice a day for 12 weeks of an AB intervention [16] or 10–15 min once a day for 9 months [18], it is possible to get the above effects of long duration. Most studies included in this review were performed in Australia and the USA; only one study was performed in Italy [19]. The purpose of this study protocol is to outline the design, procedures and methods used in the Imola Active Breaks study (I-MOVE study). Our study is one of the first that concerns ABs intervention carried out in an Italian setting with a two-year follow-up and with a multidisciplinary team that manages the different time assessments for multiple outcomes. Furthermore, to our knowledge, the I-MOVE protocol is the first that includes HIIT exercises within the exercise protocol. The I-MOVE study could provide key recommendations for using these interventions in the organization of Italian schools setting.

### Aims of the I-MOVE Study

1. To evaluate the effects of an active breaks intervention in increasing total day and school day PA and reducing time spent in sedentary habits in children attending primary school; the relationship between objective and reported measures of PA and health-related fitness will be examined.

2. To assess the possible effect of active breaks in improving quality of life in children, stratified by anthropometric evaluation, diet habit, socioeconomic status and parent-perceived children’s quality of life.

3. To investigate the effects of active breaks as a strategy to change the time-on-task behavior and the cognitive function of children (executive functions and multisensory perception).

4. To investigate the possible effects of active breaks in improving the development of fine and gross motor control, quantified using wearable sensors.

## 2. Materials and Methods

### 2.1. Study Design

The I-MOVE study is a school-based intervention study with a quasi-experimental design (controlled studies in which exposure was assigned by the investigator without using randomization) [20]. The current project was based on a feasibility pilot study [21] and a meta-analysis on the evaluation of school-based interventions [17]. Findings from both were used to design, structure, manage and organize the I-MOVE study. This intervention trial follows the guidelines of the SPIRITS (Standard Protocol items for intervention trials) Checklist.

The I-MOVE study was endorsed by the University of Bologna (Italy).

The administration of the study was designed to allow effective collaboration and communication among different departments of the University of Bologna.

The study was approved by the University of Bologna Bioethics Committee, on the 18th March 2019 (Prot. n. 0054382 of 18/03/2019-[UOR: SI017107-Classif. III/13]). The study was conducted following the Declaration of Helsinki and approved by the school board.

### 2.2. School and Participant Recruitment

The study setting was a primary school in the city of Imola (70,075 inhabitants, Bologna, Northern Italy).

Invitation letters accompanied by an expression of interest form were sent to the principals of 4 schools of the city of Imola. One school expressed interest in participating in the project. After that, a member of our team visited the interested school to give a global view of the project in front of the relevant staff. Furthermore, a specific meeting with the headmaster was held to obtain the school’s agreement. Finally, we organized a presentation day to explain the project to the teachers. Ten teachers of 5 classes out of 15 agreed to be involved in the project. They attended a training course of 8 h to learn the basis of the project and the practical part of the active breaks intervention. The parents of the children received a short brochure describing the study, and an invitation to attend an informative meeting at school. The purpose of the meeting was to explain the intervention that would be carried out in the classrooms. At the end of the meeting informed consent was obtained from parents/tutors.

The I-MOVE study established the following inclusion criteria: (i) studying in 1st to 5th grade (aged 6–11 years), (ii) not having health problems or physical disability, which might limit the performance of ABs and (iii) having obtained informed consent of parents and permission for personal data processing.

Finally, 153 children were enrolled in the study (Figure 1). The mean number of children in the classes was 22. Participants were free to retire from the study at any point without giving explanations.

### 2.3. Sample Size

Sample size was estimated considering the actigraph accelerometers as a primary outcome measure of the study. Sample size calculations were based on the pilot and feasibility study [21], which detected a mean difference of 98.1 min in weekly total MVPA, measured using the accelerometer, between the intervention group and control group.

Considering an alpha error of 0.05 and a power of at least 0.8, the minimum size of the sample was estimated as 48 participants per group, for a total of 96 participants, without considering the nested data structure. Power analysis was carried out with Clinicalc.com.

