### 2.4. Intervention

The I-MOVE protocol was developed and tested, based on a previous pilot and feasibility study [18]. Some exercises of the I-MOVE protocol were implemented and suggested by the teachers of the previous Valsamoggia study [21].

The experimental groups performed the I-MOVE protocol thrice a day without a fixed time: usually two breaks in the morning and one in the afternoon every weekday. Active breaks were performed in addition to the normal recess breaks time. In particular, children got up from their chair, placed it under the desk to ensure their safety and positioned themselves to the side or behind their seat, depending on the type of exercises. Approximately every child needed 1-m diameter of free space around to perform exercises in safety.

Each active break consisted of 10 min, divided into three different parts (Table 1). The first part, called “warm-up” (2 min), focused on cardiorespiratory and mobility exercises to prepare children to increase their motor activity intensity. In the central part, called “tone up” (5 min), teachers conducted exercises with high-intensity interval training (HIIT), consisting of 40 s of vigorous PA alternated with 20 s of recovery, with a specific focus on coordination and balance. During the tone-up the children could experiment with and learn basic motor skills such as jumping and throwing. In the last part of the active break, called “cool-down” (3 min), children performed stretching, relaxation and breath control exercises. Following these exercises the children were recharged to restart the academic lesson.

The teachers could decide together with the pupils which daily exercises they liked to perform, trying to use the whole range of exercises and varying them as much as possible to keep up the enjoyment and motivation of the children. Furthermore, this modality allowed teachers to adapt the active breaks protocol according to the needs of their class, for example not using contact exercises in particular cases. Clearly, the I-MOVE protocol, performed for 10 min three times a day for every day of the week, takes time away from the curricular lessons. However, these interventions appear to benefit the classroom behavior by improving children’s attention and making teachers easier to do their jobs [22,23].

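### The sample size of 48 per group reaches power 0.8 only if children within a class are uncorrelated; the 153 enrolled keep 0.8 only up to an ICC of about 0.03

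*Protocol article*

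**What the plan says.** Section 2.3 (Sample Size) takes accelerometer-measured activity as the primary outcome measure. The effect comes from the pilot, which "detected a mean difference of 98.1 min in weekly total MVPA" between the groups. The error rates are set by "Considering an alpha error of 0.05 and a power of at least 0.8", and the result is "48 participants per group, for a total of 96 participants, without considering the nested data structure". The section states no SD and no ICC.

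Section 2.2 describes the structure that the calculation leaves out. Classes entered the intervention through their teachers: "Ten teachers of 5 classes out of 15 agreed to be involved in the project". It adds: "The mean number of children in the classes was 22". In all, 153 children were enrolled. The text does not say how many classes they came from or how they divide between the groups; the flow chart in Figure 1 is not available in the copy reviewed. Section 2.4 has teachers conducting the breaks with the whole class.

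**The concern.** Children in one class share a teacher, a timetable, a room and the way the breaks are delivered. Their weekly MVPA is therefore likely to be positively correlated, and each further child in a class adds less information than an independent child would. A sample size that treats children as independent overstates power whenever that correlation is above zero. Section 2.3 acknowledges that it did this but still gives 0.8 as the only power figure, and nothing elsewhere in the article says how far power falls.

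This matters most for a null result on the primary measure. Read against 80% power, it would look like evidence that the breaks do not add 98.1 min/week. If the real power is nearer one half, the same result says little, and a reader could not tell absence of effect from too few classes.

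**Working it through.** **Inputs from the article.** Difference 98.1 min/week, alpha 0.05, power 0.80 and 48 per group (section 2.3); mean class size 22 and 153 enrolled (section 2.2).

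**Assumptions.** Two-sided test; normal approximation unless stated; ICC from 0.01 to 0.10, because the article gives none; equal split of the 153, because the article gives no split; all children supply data.

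**1. The plan's own figure.** Without an SD, 48 per group cannot be reproduced independently, only inverted:

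SD = 98.1 / [(1.960 + 0.842) × √(2/48)] = 171.5 min/week, a standardised difference of 98.1/171.5 = 0.57.

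With this SD the formula returns 48 per group and power 0.800. That is circular and shows only that the inputs are compatible. Because 48 is rounded up, any SD from 169.7 to 171.5 fits; the lower end raises the 48-per-group powers below by about one percentage point at most.

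**2. Allowing for classes.** Design effect DE = 1 + (22 − 1) × ICC. Standard error = 171.5 × √[DE × (1/n₁ + 1/n₂)]. Power = Φ(98.1/SE − 1.960).

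| ICC | DE | Power, 48 per group | n per group for 0.80 (48 × DE) | Power, 153 split equally |
|---|---|---|---|---|
| 0 | 1.00 | 0.80 | 48 | 0.94 |
| 0.01 | 1.21 | 0.72 | 59 | 0.90 |
| 0.02 | 1.42 | 0.65 | 69 | 0.84 |
| 0.05 | 2.05 | 0.50 | 99 | 0.70 |
| 0.10 | 3.10 | 0.36 | 149 | 0.52 |

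Example at ICC 0.05 with 48 per group: SE = 171.5 × √(2.05 × 2/48) = 50.1; 98.1/50.1 − 1.960 is about 0; power is about 0.50.

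**3. How much ICC the 153 can absorb.** An equal split gives 76.5 per group. Power stays at 0.80 while DE ≤ 76.5/48 = 1.59, that is ICC ≤ 0.59/21 = 0.028. An unequal split lowers this limit; 110 against 43, taken only as an illustration, brings it to about 0.014.

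**4. Few classes.** The design-effect formula with a normal reference is optimistic when classes are few. Using a noncentral t with (number of classes − 2) degrees of freedom:

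- 7 classes of about 22, split 4 v 3 (87 and 66 children, 5 df): power 0.72 at ICC 0.01, 0.51 at 0.05, 0.36 at 0.10.
- 10 classes averaging 15.3 enrolled, split 5 v 5 (8 df): power 0.83, 0.66 and 0.51 at the same ICCs.

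Both class counts are illustrations. The first follows from 153/22 ≈ 7; the second allows for classes in which not every child was enrolled.

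**The case against.** The strongest reply is that section 2.3 discloses its limit. It presents 48 as a minimum obtained "without considering the nested data structure", and enrolment then exceeded the minimum by 59% (153 against 96). Much of this stands. Nothing is concealed, and no stated number is shown to be miscalculated, so this is not an arithmetic error. At ICC 0.01 or 0.02 the 153, split equally, keep power above 0.80 under the usual design effect. The disclosure still leaves 0.8 as the only figure and does not say what it becomes once classes are considered.

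Section 2.6.1 also plans ANCOVA, which could recover precision. If baseline MVPA were a covariate with a correlation of 0.5 (neither is stated), the residual variance factor would be 0.75 and the 153 would reach about 0.81 at ICC 0.05 by the normal approximation. That is a reason to redo the calculation with stated inputs; it does not support the present figure.

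Three stronger readings are tempting and are not supported:

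- A reader might infer that the trial falls short under any realistic class effect. The article gives no ICC, so what is realistic is an assumption, and the 153 meet 0.80 over the lower part of the range.
- A reader might infer that five full intervention classes (110 children) leave only 43 controls, below the planned 48. The text gives neither the split nor the number enrolled per class.
- A reader might add up the break schedule ("consisting of 40 s of vigorous PA alternated with 20 s of recovery", plus warm-up) and conclude that 98.1 min/week is more than the breaks can supply. The pilot difference is in total weekly MVPA, and aim 1 covers activity over the whole day, so activity outside the breaks can contribute.

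**Conclusion.** The point holds, limited to the power statement. As written, 0.8 with 48 per group is the power of a trial of independent children. For classes of 22 it falls to between 0.72 and 0.36 over ICC 0.01 to 0.10. The 153 enrolled, split equally, give between 0.90 and 0.52 over the same range and cross below 0.80 at an ICC of about 0.028. With class-level degrees of freedom, power at ICC 0.05 is about 0.51 for 7 classes (4 v 3) or 0.66 for 10 classes (5 v 5).

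These figures rest on an SD back-solved from the plan's own result, a true difference of 98.1 min/week, a two-sided unadjusted comparison, no loss of data, and an ICC, split and class count that the text does not give. The direction does not depend on the choice of ICC: any positive value takes 48 per group below 0.80 with the implied SD of 171.5. The size of the shortfall for the 153 does depend on these inputs, which is why a range should be reported.

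**What to change.** In section 2.3:

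1. State the pilot SD used, and whether the test is two-sided.
2. Say that 48 per group gives power 0.8 only at ICC 0.
3. Replace the 0.8 claim with the power, or the minimum detectable difference, of the 153 enrolled. Use the actual number and size of classes in each group and class-level degrees of freedom, over ICC 0.01 to 0.10. If a baseline-adjusted analysis is assumed, state the correlation used.

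The cost is a recalculation and a few sentences. No extra enrolment is needed, and no estimate or test changes. The downside is that the stated power becomes less favourable, and a null primary result would have to be interpreted accordingly.

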### 2.4. Intervention

The I-MOVE protocol was developed and tested, based on a previous pilot and feasibility study [18]. Some exercises of the I-MOVE protocol were implemented and suggested by the teachers of the previous Valsamoggia study [21].

The experimental groups performed the I-MOVE protocol thrice a day without a fixed time: usually two breaks in the morning and one in the afternoon every weekday. Active breaks were performed in addition to the normal recess breaks time. In particular, children got up from their chair, placed it under the desk to ensure their safety and positioned themselves to the side or behind their seat, depending on the type of exercises. Approximately every child needed 1-m diameter of free space around to perform exercises in safety.

Each active break consisted of 10 min, divided into three different parts (Table 1). The first part, called “warm-up” (2 min), focused on cardiorespiratory and mobility exercises to prepare children to increase their motor activity intensity. In the central part, called “tone up” (5 min), teachers conducted exercises with high-intensity interval training (HIIT), consisting of 40 s of vigorous PA alternated with 20 s of recovery, with a specific focus on coordination and balance. During the tone-up the children could experiment with and learn basic motor skills such as jumping and throwing. In the last part of the active break, called “cool-down” (3 min), children performed stretching, relaxation and breath control exercises. Following these exercises the children were recharged to restart the academic lesson.

The teachers could decide together with the pupils which daily exercises they liked to perform, trying to use the whole range of exercises and varying them as much as possible to keep up the enjoyment and motivation of the children. Furthermore, this modality allowed teachers to adapt the active breaks protocol according to the needs of their class, for example not using contact exercises in particular cases. Clearly, the I-MOVE protocol, performed for 10 min three times a day for every day of the week, takes time away from the curricular lessons. However, these interventions appear to benefit the classroom behavior by improving children’s attention and making teachers easier to do their jobs [22,23].

Active breaks are also reported by the teachers themselves as a useful strategy for optimizing the time dedicated to academic lessons in particular because active breaks are able to energize children who have difficulty in maintaining concentration during daily school activities [19,21].

### 2.5. Data Collection and Outcome Measures

During the Imola Active Breaks Study the following outcomes will be evaluated: (1) PA and sedentary behaviors; (2) health related fitness; (3) motor control development during fine and gross (locomotor) tasks; (4) dietary patterns; (5) anthropometric evaluation; (6) sociodemographic and early determinants; (7) cognitive Function; (8) time-on-task behavior and (9) quality of Life.

As shown in Table 2, all the measurements will be evaluated at baseline T0 (October 2019) and will then be assessed at mid-intervention T1 (October 2020) and at the end of the intervention T2 (June 2021) to investigate group differences and changes over time. The process evaluation will performed 6 months after the end of the intervention T3 (December 2021.)

The comparisons between T0, T1 and T2 will allow the research to determine the timing of any long-term effect of ABs and whether the effects of ABs are cumulative in time or reach a ceiling after T1 (for example, if there are cumulative effects, then performance should reveal a pattern T0 < T1 < T2; by contrast, if they reach positive effects in a few months and then stabilize, then performances at T1 and T2 should not differ).

Moreover, we planned an assessment at the mid-intervention to measure an acute effect before the daily active breaks and immediately after the 10-min bout for cognitive and time on task outcomes. During this specific mid-intervention we will monitor the amount of PA performing an active break, 10 min thrice a day, during a school day for a week. This assessment will be focused on cognitive function and time-on-task behaviors, since these could be more affected after acute exercises than chronic ones, as shown for some cognitive functions in the literature [24,25,26].

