## Figures and Tables

**Figure 1 ijerph-17-06123-f001:**
[figure not shown]
Flow chart of the I-MOVE study.

**Table 1 ijerph-17-06123-t001:** Components of I-MOVE protocol.

Phase	Aim	Examples of the Type of Exercises	Duration
Warm-up	Cardiorespiratory and mobility exercises	“The chair march”: The children all stand up and move their chairs sideways, waiting for the teacher’s commands. They begin to march, raising their knees well and resting their toes on the chair, without pushing upwards. Progressively, they also combine the movement of the legs with the alternating movement of the arms.	2 min
Tone-up	High-intensity interval training (HIIT) exercises	HIIT Animal jumps: Children scattered around the classroom have to jump like frogs for 40 s then rest for 20 s and repeat the exercise 2 times, then they jump like kangaroos for 40 s with 20 s break to be performed 2 times.	5 min
Cool-down	Breath and relaxation exercises	The imaginary balloon: Children must inflate an imaginary balloon by inhaling and exhaling, mimicking the progressive expansion of the balloon with the widening of their arms. We ask for a very slow and long exhalation twice as long as the inspiration.	3 min

**Table 2 ijerph-17-06123-t002:** The Imola Active Breaks Study data collection and outcome measures.

Outcome Measures	Baseline October 2019 (T0)	Mid-Intervention October 2020 (T1)	End of Intervention June 2021 (T2)	6 Months After End of Intervention December 2021 (T3)
Personal information (Age, Country)	√		√	
PA and sedentary behavior (accelerometer)	√	√	√	
Total reported physical activity Questionnaire	√	√	√	
Health related fitness	√	√	√	
Motor control development	√	√	√	
Dietary patterns	√	√	√	
Anthropometric evaluation	√	√	√	
Sociodemographic and early determinants	√		√	
Cognitive Function	√	√	√	
Time-on-task behavior (Teachers and children self-administrated questionnaire)		√	√	
Quality of Life	√	√	√	
Process evaluation focus group with children				√
Process evaluation: focus group with teachers				√

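### Outcome visits at months 0, 12 and 20 can show change or plateau after T1, but cannot locate onset within the first 12 months

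*Protocol article*

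**What the plan says.** Section 2.5 sets the schedule: "all the measurements will be evaluated at baseline T0 (October 2019"), then "will then be assessed at mid-intervention T1 (October 2020"), then "at the end of the intervention T2 (June 2021) to investigate group differences and changes over time". Table 2 agrees, and its column "Mid-Intervention October 2020 (T1") is the only one between baseline and the end of the intervention.

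The same section says what the schedule is for: "The comparisons between T0, T1 and T2 will allow the research to determine the timing of any long-term effect of ABs". The sentence goes on to ask whether effects accumulate or level off after T1. A parenthesis introduced as an example gives two patterns. Cumulative effects should show as T0 < T1 < T2. For the alternative it says: "if they reach positive effects in a few months and then stabilize, then performances at T1 and T2 should not differ".

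The Introduction summarises earlier evidence as effects obtained "with 10 min thrice a day for 12 weeks of an AB intervention [16"], or with one daily break over 9 months.

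**The concern.** The stated purpose includes timing, and the plateau example is tied to gains made within a few months. The first outcome measurement after baseline comes a full year later. Both intervention lengths cited in the Introduction, 12 weeks and 9 months, are shorter than that interval. If T1 and T2 turn out alike, Section 2.5 invites the reading that benefit arrived early and then held, although nothing measured in the first year would support it.

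A second risk follows from the same wording. Failing to find a T1-T2 difference is easily taken as evidence of a plateau, when it may only reflect an imprecise comparison.

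**Working it through.** **1. Calendar.** Inputs are the dates in Section 2.5 and Table 2.

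- T0, October 2019 = month 0
- T1, October 2020 = month 12
- T2, June 2021 = month 20 (12 + 8)
- T3, December 2021 = month 26 (20 + 6)

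The text does not state when the breaks began, and Figure 1 is not shown, so counting exposure from October 2019 is an assumption. A later start would shorten exposure before T1 but would add no measurement between T0 and T1.

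**2. Does anything else fill the first year?** The acute assessment in Section 2.5 is itself placed at mid-intervention and compares before with after a single 10-minute bout. The two-monthly teacher reports in Section 2.7 concern compliance with the breaks. T3, "6 months after the end of the intervention T3 (December 2021"), is process evaluation by focus group. None of these is a child outcome measured between months 0 and 12.

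**3. What the three visits can separate.** Take the group effect as a fraction of its full size. The curve shapes are illustrative.

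| Course of the effect | Month 3 | T0 | T1 | T2 |
|---|---|---|---|---|
| Full by month 3 | 1.00 | 0 | 1 | 1 |
| Full by month 6 | 0.50 | 0 | 1 | 1 |
| Linear to month 12 | 0.25 | 0 | 1 | 1 |
| Abrupt onset at month 11 | 0.00 | 0 | 1 | 1 |
| Linear to month 16 | 0.19 | 0 | 0.75 | 1 |
| Linear to month 20 | 0.15 | 0 | 0.60 | 1 |

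The first four rows differ widely at month 3 but have identical expected values at every visit, so no sample size or model can tell them apart. The last two rows differ from the first four at T1, so growth past month 12 is distinguishable in principle.

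**4. How well could further growth be seen?** This step is illustrative. Assumptions:

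- Full effect 0.57 SD. The protocol gives no SD. Its 48 per group, difference of 98.1 min, alpha 0.05 (taken as two-sided) and power 0.8 imply SD = 98.1 / [(1.96 + 0.84) × √(2/48)] ≈ 171.5 min, and 98.1 / 171.5 ≈ 0.57.
- 76 children per group, about half of the 153 enrolled. The split is not stated in the text.
- T1-T2 correlation r of 0.5 to 0.7, equal SD at both visits, complete data, no class effect.

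Standard error of the between-group difference in T2-T1 change, in SD units: √[2(1 − r)] × √(2/76).

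- r = 0.5: 1.000 × 0.162 = 0.162
- r = 0.7: 0.775 × 0.162 = 0.126

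For linear growth to month 20 the change from T1 to T2 is (1 − 0.60) × 0.57 = 0.228 SD. Two-sided power at 0.05 is approximately Φ(0.228/SE − 1.96).

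- r = 0.5: Φ(1.41 − 1.96) = Φ(−0.55) ≈ 29%
- r = 0.7: Φ(1.81 − 1.96) = Φ(−0.15) ≈ 44%

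The 95% interval half-width is 1.96 × SE, about 0.25 to 0.32 SD, which is larger than the 0.228 SD change itself.

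**The case against.** The strongest reply is that the sentence has been read too narrowly. It also asks whether effects accumulate or reach a ceiling after T1, and visits at 12 and 20 months address that in principle. This stands, and it limits the point to onset before T1. A reader might infer that the schedule says nothing about timing, but rows five and six of the table show otherwise.

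A reader might also take the parenthesis as a decision rule under which equal T1 and T2 values prove early benefit. The text does not say that. It is a forward prediction offered as an example, it is correct in that direction, and Section 2.6.1 contains no decision based on it. The reverse inference is a risk that the wording creates, not a step that the protocol commits to.

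Two further inferences should not be drawn. One is that the design fails because it would miss an effect that fades before month 12: the stated aim concerns long-term effects, and such an effect is not one. The Introduction's 12 weeks and 9 months are durations of earlier interventions and do not define a window that this study undertook to observe. The other is that the T1-T2 pattern will determine advice on how long schools should run breaks: the Introduction speaks only generally of recommendations for using such interventions.

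The power figures are also open to challenge, since effect size, group sizes and correlation are all assumed. That is fair. They bear only on reading a non-significant T1-T2 difference, and the argument about onset does not use them.

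**Conclusion.** The point holds in a limited form. With outcomes at months 0, 12 and 20, the protocol can address whether a group difference is present by month 12 and whether it changes by month 20. It cannot determine when within the first 12 months an effect arose, so both the general claim about timing and the link between a plateau and the first few months go beyond the design. This conclusion follows from the dates alone, with October 2019 assumed as the start.

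A non-significant T1-T2 difference does not establish a ceiling. Under the stated assumptions, an effect still growing linearly at month 20 would be missed more often than found (power about 29-44%). Dependence among children in the same class would probably lower this further. These percentages are illustrations, not properties of the trial. The defect is one of stated aim and reporting, and the visit schedule itself can stand.

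**What to change.** In Section 2.5, restate the aim: the comparisons show whether a between-group difference is present by 12 months, and whether it is larger, similar or smaller at 20 months. Remove the general claim to establish timing, and in the plateau example refer to effects reached by 12 months instead of within a few months.

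Report three quantities with confidence intervals: the between-group difference at T1, the between-group difference at T2, and the between-group difference in T2-T1 change. Claim a ceiling only if the interval for the third excludes a further change judged meaningful, with that margin stated beforehand. Otherwise report that the data do not settle whether the effect levelled off. Describe onset only as by 12 months or between 12 and 20 months.

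The cost is wording, one pre-stated margin and one additional contrast from data already planned. No visit is added. The drawback is a more modest stated claim and, if the T2-T1 interval is wide, possibly no conclusion about a ceiling.
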